#### **DESCRIPTIVE STATISTICS**

Descriptive statistics will be used to describe the participant population at baseline. Participant characteristics will include: (1) Age, (2) Gender, (3) Race, (4) Ethnicity, and (5) Education Level, (6) Body Mass Index (BMI), (7) Hemoglobin A1c (HbA1c) Level, (8) Comorbidities (ie. hypertension and dyslipidemia), (9) Dietary Characteristics, (10), Physical Activity, and (11) Pharmacotherapy.

#### **SUB-GROUP ANALYSES**

Analyses will be performed within sub-groups to compare the primary outcome of absolute change in percent HbA1c and process measures of changes in VO2max and self-reported physical activity:

1. Years of age at study enrollment. 30-45 vs. 45-55 vs. 56-65
2. Gender. Male versus female.
3. Race. White vs. African American/Black vs. American Indian vs. Asian vs. Pacific Islander vs. Other
4. Ethnicity. Non-Hispanic/Latino vs. Hispanic/Latino

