## **Chapter 6: Randomization and Data Analysis Plan**

## 6.1 RANDOMIZATION

### 6.1.a RANDOMIZATION

Block Randomization is the method to be used to randomize study participants into study arms. The method is developed to pre-specify the number of arm assignments in a random order. IMPACT will utilize Block Randomization in conjunction with stratification in order to promote balance of participant characteristics within each study arm. The participant characteristics, or parameters, to be used for the IMPACT study includes: (1) age, (2) gender, and (3) HbA1c level.

Participant characteristics will be stratified as followed:

- Age (years)
  - >29.9 – 50.9 (young age)
  - 51.0 – 65.0 (older age)
- Gender
  - Male
  - Female
- HbA1c (percentage)
  - 6.6 – 7.9 (low A1c)
  - 8.00 – 9.9 (high A1c)

As a result, there are eight (8) strata in total:

1. Low HbA1c, younger age and female
2. Low HbA1c, younger age and male
3. Low HbA1c, older age and female
4. Low HbA1c, older age and male
5. High HbA1c, younger age and female
6. High HbA1c, younger age and male
7. High HbA1c, older age and female
8. High HbA1c, older age and male

Each block size will contain six (6) group assignments, evenly distributed across the three study arms. The blocks will contain random permutations (ie. 211332, 321231, etc) that are pre-determined by SAS.

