## **6.2 DATA ANALYTICAL METHODS**

### **6.2.a DATA ANALYSIS PLAN**

Statistical analyses will investigate clinical effectiveness of structured physical activity regimens across varying frequencies. The main statistical approach will be to date-match outcomes to concomitant exercise regimens, then to examine univariate and multivariate associations with changes in clinical outcomes, patient-centered outcomes, and cost. Statistical significance will be determined at  $P < 0.01$ , a stricter value due to the expected number of models used, or with other adjustments for multiple comparisons when applicable. Statistical analyses will be performed using SAS® (Cary, NC), and supplemented with STATA or Splus for methods not available in SAS®.

Study participants who are not able or willing to continue with the randomized frequency of intervention will be treated as loss to follow-up and only data obtained while in the assigned protocol will be used in the primary analysis (intention-to-treat). Since participants and non-participants continue to receive care within the healthcare system contemporaneously during the research study, IMPACT will obtain interstitial outcome data and complete clinical narrative through observational data available in the EHR. The statistical analysis will be conducted by Senior Statistician/s with the guidance of Biostatistical Consultant [name].

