## **6.2.b POWER AND SAMPLE SIZE**

The primary analyses for this study will be comparing the clinical outcomes, patient-centered outcomes, and cost effectiveness of structured exercise regimens across varying frequencies (once vs. thrice-weekly, compared to usual care). For Specific Aim 1, overall change in baseline of outcome values will be examined (e.g. HbA1c, VO2max, physical activity). By the algebraic properties of log and variance, we estimated difference in groups as  $\log(\text{HbA1c}_1) - \log(\text{HbA1c}_2) = \log(\text{HbA1c}_1 / \text{HbA1c}_2)$ , and  $\text{SD}(\log(\text{HbA1c})) = \text{SD}(\text{HbA1c}) / \text{mean}(\text{HbA1c})$ . A two-sample *t*-test between means, Bonferroni adjusted  $\alpha = 0.05/3 = 0.016$ , assuming normality of  $\log(\text{HbA1c})$ , equal group variances, and a baseline mean HbA1c of 6.5%, we will have 80% power to detect a 0.5% point difference in HbA1c with 92 patients/arm. Accounting for a 20% attrition, this will require 115/arm, 345 patients total.

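### Arms are to be compared within each subgroup level with no arm-by-subgroup interaction test named, and the printed age bands put 45-year-olds in two groups.

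*Protocol*

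**What the plan says.** The Sub-Group Analyses part of Protocol section 6.2.a states the method: "Analyses will be performed within sub-groups to compare the primary outcome of absolute change in percent HbA1c". It applies the same plan to VO2max and self-reported activity. Four factors are listed, with their levels set against each other. Age at enrolment is banded "30-45 vs. 45-55 vs. 56-65". Gender has two levels, ethnicity has two, and race has six: "White vs. African American/Black vs. American Indian vs. Asian vs. Pacific Islander vs. Other".

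The Aim 3 text in the same section also promises to examine heterogeneous effects, by gender, age and baseline condition, again through subgroup analysis and with no test named. The Aim 1 regression model has arm as the predictor of interest and patient characteristics as covariates. It mentions no product term between arm and any characteristic.

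On error control, section 6.2.a sets P<0.01 as the general level, described as "a stricter value due to the expected number of models used", and allows other multiplicity adjustments. Section 6.2.b gives the design: "we will have 80% power to detect a 0.5% point difference in HbA1c with 92 patients/arm", at a Bonferroni alpha of 0.05/3. No power is given for subgroups.

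**The concern.** A subgroup question asks whether the treatment effect differs between levels. A test inside each level asks something else: whether there is an effect in that level. A level can miss significance simply because it holds fewer patients, so one significant and one non-significant result is weak evidence that the effects differ. The protocol names the within-level analysis and nothing that compares effects between levels. A reader of the trial's results could then be told that exercise lowers HbA1c in one sex or age group and not in another when the effect is the same in both.

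The age bands raise a separate and smaller matter of definition. A person aged 45 at enrolment meets both the first and the second band, so the three groups are not a partition and their counts need not add up to the trial total.

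**Working it through.** **Inputs.** From Protocol section 6.2.b: 92 evaluable patients per arm, 80% power, a 0.5-point difference, alpha 0.05/3 (taken as two-sided). From section 6.2.a: significance at P<0.01. Assumptions: the true effect equals the design effect in every level; the sexes are split 50:50; the three age bands are of equal size and treated as disjoint; one pairwise arm contrast is considered; the normal approximation is used.

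**The plan's own figures.** The attrition step reproduces: 92 / 0.80 = 115 per arm, and 3 × 115 = 345. The 92 itself cannot be checked because no standard deviation is given. It is not needed here, since the stated power and n fix the standardised effect:

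- d = (2.394 + 0.842) × √(2/92) = 3.236 × 0.1474 = 0.477
- implied SD on the absolute scale = 0.5 / 0.477 ≈ 1.05 points

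**Two sexes, same effect.** With 46 per arm in each sex:

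- non-centrality = 0.477 × √(46/2) = 2.288
- power at 0.01 = Φ(2.288 − 2.576) = 0.387
- the sexes are independent, so P(exactly one significant) = 2 × 0.387 × 0.613 = 0.474

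A simulation of 40,000 trials using t tests gave 47%.

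**Three equal age bands, same effect.** With 92/3 = 30.7 per arm in each band:

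- non-centrality = 0.477 × √(30.7/2) = 1.87
- power at 0.01 = Φ(1.87 − 2.576) = 0.240
- P(mixed) = 1 − 0.240³ − 0.760³ ≈ 0.546

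**Sensitivity to the level used, 92 per arm:**

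| Two-sided alpha | Power per sex | Exactly one sex significant | Power per age band | Age bands mixed |
|---|---|---|---|---|
| 0.05 | 63% | 47% | 46% | 75% |
| 0.05/3 | 46% | 50% | 30% | 63% |
| 0.01 | 39% | 47% | 24% | 55% |

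A 30:70 sex split gives 53% to 56%. If all 115 per arm are retained, the ranges over these three levels are 40% to 50% for equal sexes and 65% to 74% for equal age bands.

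**No true effect.** At 0.01, P(exactly one of two significant) = 2 × 0.01 × 0.99 = 0.0198, about 2%.

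**Interaction test, same setting.** When the sexes share one effect, the test declares a difference at its nominal rate: 1% at alpha 0.01 and 5% at 0.05 (simulated 1.0% and 4.9%). For a true 0.5-point difference in effect between the sexes:

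- standardised distance = 0.477 / (√(2/46) × √2) = 0.477 / 0.295 = 1.618
- power at 0.01 = Φ(1.618 − 2.576) = 0.169
- power at 0.05 = Φ(1.618 − 1.960) = 0.366

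**Overlap at 45.** Ages 30 to 65 span 36 whole years. If ages were uniform, 1/36 = 2.8% of patients would be 45, or 345/36 ≈ 10 people. The protocol gives no age distribution, so this is only an indication.

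**The case against.** The strongest reply is that the protocol states no rule for claiming a subgroup difference. It does not say that differences will be declared from within-level p-values, and setting levels against each other is compatible with a formal contrast. A statistical analysis plan, not shown here, could add an interaction test. This stands in part. The finding must be conditional on how the separate results are read. But the protocol does not leave the method open: it names the within-level analysis and prints the levels, so naming the test that answers the question improves a stated method.

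The conditions on the size also stand. The 47% and 55% need the design effect to be present and equal in every level, and with no effect the problem almost vanishes. No hypothesis in section 2.3 concerns these subgroups, and the sample size does not rest on them.

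Three stronger readings are tempting, and the document does not support them.

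- **That the age bands themselves create false subgroup effects.** They do not. The discordance comes only from separate testing. The overlap at 45 is a distinct definition error, and the neighbouring boundary at 55/56 is disjoint.
- **That ignoring the randomisation age cut (51, section 6.1.a) is an error.** Age at enrolment is a baseline variable, so a randomised comparison within any age band is valid. Stratification adds balance, not validity. Race and ethnicity are not strata either.
- **That the plan commits to 117 tests.** There are 3 + 2 + 6 + 2 = 13 levels and three outcomes. Three pairwise contrasts would give 13 × 3 × 3 = 117 tests and about 1.2 false positives at 0.01, but the subgroup text states no contrasts, and section 6.2.a also lists ANOVA across arms. One global test each gives 13 × 3 = 39 tests and about 0.4. The plan's 0.01 level is already a multiplicity measure.

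**Conclusion.** The point holds in conditional form. The protocol plans arm comparisons inside each subgroup level and names no interaction test. If subgroup differences are inferred from those separate results, a trial whose treatment works as designed and equally in both sexes would show exactly one significant sex about 47% of the time at P<0.01, and mixed results over three equal age bands about 55% of the time. An interaction test would be wrong in 1% of such trials at the same level. These rates rest on the stated design power and the assumed subgroup shares. They do not depend on the unstated standard deviation, and they fall to about 2% for two groups if no arm differs.

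The double placement of 45-year-olds is an error in the printed bands whatever else is planned, with a small effect (about 3% of patients under a uniform age assumption). Neither matter touches the primary HbA1c comparison. What is at stake is the credibility of statements about who benefits.

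**What to change.** In Sub-Group Analyses, state that:

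- heterogeneity is judged by one arm-by-subgroup interaction test per factor, fitted in the full model on all patients;
- within-level estimates and confidence intervals are shown descriptively;
- the subgroup work is exploratory;
- the age bands are disjoint, for example 30-44, 45-55 and 56-65.

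Using the randomisation age cut at 51 is an option, not a correction.

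The cost is a few sentences, with no new data and no change in sample size. The downside is low power: about 17% at 0.01 and 37% at 0.05 to detect a 0.5-point difference in effect between two equal groups. Fewer subgroup claims will be possible, and a non-significant interaction must not be read as proof of equal effects.

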## **STUDY AIM 1: CLINICAL EFFECTIVENESS**

### **Research Questions**

1. Does a thrice-weekly, structured exercise regimen have greater reduction in HbA1c than a weekly contact exercise regimen? How do these interventions compare to usual care?
2. Are the same improvements observed for process measures (i.e., VO2 max and self-reported physical activity)?

### **Primary Outcomes and Process Measures**

Primary outcomes and process measures will be compared between the three intervention arms (weekly, thrice-weekly, usual care). Primary outcomes include absolute change in percent HbA1c, and process measures include change in VO2 max and self-reported physical activity. Adherence will be defined as attending more than 80% of assigned structured exercise sessions, and will be used as a covariate for stratification or adjustment.

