#### **Arm 3: Usual Care (Control Group)**

The third arm of the IMPACT study does not required study participants to attend any group exercise sessions. Study participants are to continue with current T2DM management and seek care from their personal healthcare provider. Study participants within this study arm are expected to attend a total of six study visits.

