#### **Clinical Effectiveness**

1. By the end of Phase 1, experimental study participants (Arm 1 & Arm 2) who adhered to their group exercise schedule should have greater improvements in primary outcomes compared to non-experimental study participants (Arm 3).
  - a. Improvements in primary outcomes include reduction in HbA1c levels, increase in VO2 max levels, and increase in self-reported physical activity levels.
2. By the end of Phase 1, experimental study participants who attended thrice-weekly group exercise sessions (Arm 2) should have greater improvements in primary outcomes compared to experimental study participants who attended once-weekly group exercise sessions (Arm 1).
3. By the end of Phase 2, experimental study participants (Arm 1 & Arm 2) who maintained their exercise schedule should have improved primary outcomes compared to non-experimental study participants (Arm 3).
4. By the end of Phase 2, experimental study participants who maintained thrice-weekly exercise sessions (Arm 2) should have greater improvements in primary outcomes compared to experimental study participants who maintained once-weekly exercise sessions (Arm 1).

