### **Statistical Analysis**

In univariate analyses, the percent change from baseline will be compared across intervention arms using appropriate parametric (ANOVA, *t* tests) or non-parametric (Wilcoxon) methods.

In multivariate analyses, change in outcomes will be modeled using linear regression. Percent change from baseline will be a continuous outcome with intervention arm as the predictor of interest and various participant characteristics as covariates (e.g. sex, age, race/ethnicity, anthropometry, self-reported diet and exercise, pharmacotherapy, family history, etc.). Repeated measures analysis using the outcome at different time points and mixed-effects models will also be performed. Available nonparticipants will serve as contemporaneous comparators to address possible secular trends in outcome values.

Study participants in the exercise program may also be undergoing concomitant pharmaceutical therapy to reduce HbA1c. The approach is to repeat the above analyses stratified by use of hypoglycemic medication. Another approach is to use a composite binary outcome variable for whether participants were successful in either decreasing diabetes medication or reduced HbA1c by 0.5% without increasing medications. Logistic regression will be used to assess the likelihood of achieving the composite outcome.

Study participants will be studied based on their randomized assignment (intention-to-treat). In sensitivity analyses, participants may be re-analyzed based on actualized attendance if they more closely resemble one of the other arms (once-weekly, thrice-weekly, usual care). A study participant assigned to thrice-weekly, who attends only once a week may be re-analyzed as a weekly patient. Stratification by adherent (attendance >80%) or not will also be another sensitivity analysis.

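### Adherence, which arises after randomisation and has no value in usual care, is named without restriction as a covariate for the three-arm comparison, and secondary hypotheses 1, 3 and 4 are conditioned on it

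*Protocol*

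**What the plan says.** Section 6.2.a, Study Aim 1, under Primary Outcomes and Process Measures, sets the comparison: "Primary outcomes and process measures will be compared between the three intervention arms (weekly, thrice-weekly, usual care". The same paragraph then defines adherence as "attending more than 80% of assigned structured exercise sessions, and will be used as a covariate for stratification or adjustment". Nothing there limits this to a sensitivity analysis.

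Section 2.2.a says that the usual care arm "does not required study participants to attend any group exercise sessions".

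In section 2.3.b (Clinical Effectiveness), secondary hypothesis 1 concerns exercise-arm participants "who adhered to their group exercise schedule should have greater improvements in primary outcomes compared to non-experimental study participants (Arm 3". Hypothesis 3 concerns those "who maintained their exercise schedule should have improved primary outcomes compared to non-experimental study participants (Arm 3". Hypothesis 4 sets Arm 2 participants who maintained thrice-weekly sessions against Arm 1 participants who maintained once-weekly sessions.

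The Statistical Analysis text of Study Aim 1 says that participants are studied by randomised assignment and calls this intention-to-treat. As sensitivity analyses it adds that "participants may be re-analyzed based on actualized attendance if they more closely resemble one of the other arms", with the example of a thrice-weekly participant "who attends only once a week may be re-analyzed as a weekly patient", and a stratification by adherent or not.

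**The concern.** Attendance is a consequence of the assigned arm and, in all likelihood, of motivation, health and diet. Those factors may themselves influence HbA1c. Putting attendance into the model that compares arms, or selecting on it in one arm, gives up the protection of randomisation: a difference can appear with no exercise effect, or a real effect can be hidden.

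There is also a problem of definition. Percentage of assigned sessions attended is zero divided by zero in Arm 3, and the protocol gives no code for it. If Arm 3 is left missing, it drops out of the adjusted model. If it is coded all adherent or all non-adherent, the arm coefficient becomes a comparison of controls with only the adherers, or only the non-adherers, of an exercise arm.

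At stake is whether the answers on exercise versus usual care, and on once- versus thrice-weekly exercise, can be read as effects of assignment. An analysis plan that follows this text would inherit two incompatible instructions.

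**Working it through.** **The plan's own figure.** Section 6.2.b gives 92 per arm for a 0.5-point difference, 80% power and alpha 0.05/3 (0.0167, printed 0.016). Attrition reproduces: 92/0.80 = 115, and 3 x 115 = 345. No SD is stated. Solving back (two-sided, which is assumed), SD = 0.5 x sqrt(92/2)/(2.394 + 0.842) = 1.05; a t-test on the log scale gives about 1.00. An SD of 1.0 is thus in line with the design. The point does not depend on this figure.

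**Closed-form illustration, no true effect.** Assumed, because the protocol gives neither: share adherent q = 0.6, and adherers' HbA1c lower than non-adherers' by g = 0.3 point for reasons other than exercise. Let the mean in every randomised arm be m.

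- Adherers' mean is m - (1 - q)g; non-adherers' mean is m + qg.
- Adherers minus all controls (the form of hypothesis 1): -(1 - q)g = -(0.4)(0.3) = -0.12.
- Adjusted arm effect, controls coded non-adherent: +qg = (0.6)(0.3) = +0.18.
- Adjusted arm effect, controls coded adherent: -(1 - q)g = -0.12.
- Type I error of adherers versus controls: 92 x 0.6 = 55.2 adherers against 92 controls, SE = sqrt(1/92 + 1/55.2) = 0.170, shift 0.12/0.170 = 0.70 SE, critical value 2.394. The rejection rate is about 4.7% against a nominal 1.67%.
- With g = 0.5: bias -0.20, rejection rate about 11%.
- With g = 0: no bias anywhere.

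**Simulation, no true effect.** 92 per arm, SD 1.05, two-sided alpha 0.05/3, 3,000 runs. Attendance is correlated with a prognostic factor. Assumed adherent shares are 70% in Arm 1 and 50% in Arm 2; Arm 3 is coded non-adherent. Cells show bias in HbA1c points and rejection rate.

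| Analysis | Correlation 0.2 | 0.3 | 0.5 |
|---|---|---|---|
| Arm 2 vs Arm 3 as randomised | 0.00; 1.8% | 0.00; 1.5% | 0.00; 2.0% |
| Adherent Arm 2 vs all Arm 3 | -0.17; 7% | -0.25; 14% | -0.42; 45% |
| Arm 2 vs Arm 3, adjusted for adherence | +0.17; 7% | +0.26; 19% | +0.43; 56% |
| Adherent Arm 2 vs adherent Arm 1 | -0.07; 2% | -0.09; 3% | -0.16; 7% |
| All Arm 2 non-adherers moved to Arm 1, Arm 2 vs Arm 1 | -0.23; 13% | -0.33; 30% | -0.56; 79% |

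At correlation 0 no analysis is biased. With shares of 80% and 60% and correlation 0.3, rows two, three and five give -0.20 (10%), +0.32 (25%) and -0.29 (25%). Row four stands in for the shape of hypothesis 4, with selection on both sides: the bias is smaller but does not vanish when the selected shares differ. Row five moves every non-adherer, a harder rule than the protocol's resemblance criterion. It bears only on an analysis labelled as sensitivity.

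**The case against.** The strongest defence is that the two parts of Study Aim 1 should be read together. The Statistical Analysis text makes analysis by randomised arm the main one. Its list of example covariates does not include adherence, and the only adherence analysis it specifies is a sensitivity stratification. The primary hypothesis in section 2.3.a is not conditioned on adherence; the conditioned ones are all secondary. This stands and limits the point. It does not remove it: the covariate list is open-ended, and the adherence sentence sits in the definition of the three-arm comparison and says adjustment without qualification.

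The size rests on assumed inputs, and the alpha comes from the power section. At the P < 0.01 threshold in section 6.2.a, the same approximation gives about 3.1% and 8.1% against a nominal 1%. That too stands.

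A reader might infer two stronger things that the protocol does not support:

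- That moving participants between arms by attendance distorts the main once- versus thrice-weekly answer. It is optional and labelled a sensitivity analysis, so it leaves a comparison run by randomised arm untouched.
- That the sentence "The main statistical approach will be to date-match outcomes to concomitant exercise regimens" makes the regimen actually followed the main exposure. Elsewhere (section 2.2.c and the Aim 1 research questions) the protocol uses regimen for an arm's programme, so the sentence may only align outcome dates with that programme.

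Nor does hypothesis 4 compare maintainers with a whole arm: both of its sides are selected, and the -(1 - q)g formula does not apply to it.

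**Conclusion.** The point holds in this form. The protocol permits, without restriction, adjustment of the three-arm comparison for a post-randomisation variable that is undefined in usual care. Secondary hypotheses 1, 3 and 4 are framed as non-randomised contrasts, contrary to the protocol's own intention-to-treat statement.

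That the variable has no value in Arm 3, and that the hypotheses are conditioned, follows from the text alone. The bias requires attendance to be related to prognosis. Under the stated assumptions it runs from 0.12 point in the base illustration to about 0.25 point at a correlation of 0.3 (Arm 2 versus usual care, 70%/50% adherent), against a design difference of 0.5 point, and its sign depends on the analysis and on the coding. It is zero if attendance carries no prognostic information; the protocol gives no basis for relying on that.

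Severity: should be fixed. The main comparison is safe if it is run by randomised arm without adherence in the model.

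**What to change.** - In section 6.2.a, Primary Outcomes and Process Measures, keep the definition of adherence but delete everything after the comma in "attending more than 80% of assigned structured exercise sessions, and will be used as a covariate for stratification or adjustment", so that adherence does not enter the arm-comparison models.
- In section 2.3.b, reword clinical-effectiveness hypotheses 1, 3 and 4 to compare the arms as randomised.
- In the Statistical Analysis text, keep the attendance-based re-analyses only as supportive, non-randomised analyses, and state that they cannot change the conclusion on once- versus thrice-weekly exercise.
- Report attendance descriptively for Arms 1 and 2.
- Optionally, add a complier-average estimate of each exercise arm versus usual care as a supportive analysis. State its exclusion assumption as doubtful, because exercise-arm participants also receive an exercise handbook (section 3.2.b), evaluations and a resistance band (section 4.2.a). It does not answer the once- versus thrice-weekly question.

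The cost is wording and at most one extra model. Attendance is already recorded (sections 4.1.b and 4.1.c), and the total of 345 is unchanged.
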